## Abstract

**Background:**

Bladder health is an understudied state and difficult to measure due to lack of valid and reliable instruments. While condition specific questionnaires assess presence, severity and degree of bother from lower urinary tract symptoms, the absence of symptoms is insufficient to assume bladder health. This study describes the methodology used to validate a novel bladder health instrument to measure the spectrum of bladder health from very healthy to very unhealthy in population based and clinical research.

**Methods:**

Three samples of women are being recruited: a sample from a nationally representative general population and two locally recruited clinical center samples—women with a targeted range of symptom severity and type, and a postpartum group. The general population sample includes 694 women, 18 years or older, randomly selected from a US Postal delivery sequence file. Participants are randomly assigned to electronic or paper versions of the bladder health instrument along with a battery of criterion questionnaires and a demographic survey; followed by a retest or a two-day voiding symptom diary. A total of 354 women around 7 clinical centers are being recruited across a spectrum of self-reported symptoms and randomized to mode of completion. They complete the two-day voiding symptom diary as well as a one-day frequency volume diary prior to an in-person evaluation with a standardized cough stress test, non-invasive urine flowmetry, chemical urine analysis and post void residual measurement. Independent judge ratings of bladder health are obtained by interview with a qualified health care provider. A total of 154 postpartum women recruited around 6 of the centers are completing similar assessments within 6–12 weeks postpartum. Dimensional validity will be evaluated using factor analysis and principal components analysis with varimax rotation, and internal consistency with Cronbach’s alpha. Criterion validity will be assessed using multitrait-multimethod matrix including correlations across multiple data sources and multiple types of measures.

**Discussion:**

We aim to validate a bladder health instrument to measure the degree of bladder health within the general population and among women (including postpartum) recruited from local clinical centers.

*Trial registration* NCT04016298 Posted July 11, 2019 (https://www.clinicaltrials.gov/ct2/show/NCT04016298?cond=bladder+health&draw=2&rank=1).

## Background

Methods to promote bladder health and prevent lower urinary tract symptoms (LUTS) are poorly understood and strategies for decreasing risk of LUTS across the lifespan of girls and women are lacking. In order to better understand the impact of bladder health promotion and LUTS prevention strategies, valid measures for assessing bladder health are urgently needed. Historically, and like most medical conditions, bladder health has been assumed through the presence or absence of symptoms. Existing instruments have been primarily designed to measure LUTS and assess impact of interventions in clinical populations or the burden of disease in epidemiologic studies. While reports of “normative data” and “healthy function” have been published, these are limited by the fact that the study populations are typically poorly characterized with respect to bladder health and described as “normal”, “healthy”, or “asymptomatic” based purely on the absence of LUTS [1–3]. Additionally, while there are numerous terms and definitions to describe bladder disease, a definition and measure of bladder health did not previously exist. Thus, a true estimate of women’s bladder health in the general population is currently not attainable.

The Prevention of Lower Urinary Tract Symptoms (PLUS) Research Consortium was established in 2015 with the primary charge of identifying and promoting bladder health (BH) [4]. By employing a rigorous prevention-based research agenda, the ultimate goal is to understand how to promote and preserve bladder health and prevent LUTS over the life course of girls and women [5, 6]. Essential toward this aim is an assessment of the distribution of bladder health in the general population. An initial step in the process was to establish a formal definition of bladder health for use in the development of a valid measure [7]. Consistent with the World Health Organization’s definition of health [8]. The PLUS Consortium conceptualizes bladder health as *“*a complete state of physical, mental, and social well-being related to bladder function, and not merely the absence of lower urinary tract symptoms (LUTS). Healthy bladder function permits daily activities, adapts to short term physical or environmental stressors, and allows optimal well-being (e.g., travel, exercise, social, occupational or other activities)” [9].

Measuring degrees of bladder health in a variety of settings requires a valid instrument, ideally self-administered, that can capture a spectrum from very healthy to very unhealthy. The PLUS bladder health item pool was generated using expert opinion, review and adaptation of existing instruments, and drafting of novel items to assess the elements of our conceptual model of bladder health. This content valid item pool is referred to as the Bladder Health Instrument (BHI), with the aim of further development and evaluation to result in a Bladder Health Scale (BHS). The BHI items and language were further refined by cognitive evaluation with community dwelling women and review of focus group data, as the initial step in scale development [10]. The primary objective of this paper is to describe the methodology employed by the PLUS Research Consortium for scale development and further scale evaluation, including: (1) assess the reliability and validity of the PLUS-BHI for measurement of bladder health among adult women and (2) evaluate effects of mode of administration of the PLUS-BHI in order to create a scale that is mode agnostic. This will support its use in future research in population-based national studies and future prevention trials.

## Methods/design

### Overview

The Validation of Bladder Health Instrument for Evaluation in Women (VIEW) study is an IRB approved (ADVARRA #Pro00032238), multicenter study funded by the National Institute of Diabetes and Digestive and Kidney Diseases (NIDDK) (NCT04016298), designed to test a questionnaire that can measure the degree of bladder health in epidemiologic research conducted across different populations and recruitment strategies as well as for use in local community intervention studies. The VIEW study builds upon the internal validation of the item pool for the instrument by evaluating dimensional validity and internal reliability and further establishes external validity. The goal is to create a Bladder Health Scale (PLUS-BHS) to establish basic inferential validity and to draw valid inferences about the distribution of bladder health in women in the general population and also in clinical research. Therefore, it is essential that the populations represented in the validation samples have some equivalence to the target populations the PLUS-BHI is intended to be used in [11]. The VIEW study protocol includes three population samples: a sample from a nationally representative general population and two locally recruited clinical center samples—women with a targeted range of symptom severity and type, and a postpartum group. Postpartum women are a focal population identified for future research due to the known high risk of developing LUTS in the peripartum period and evidence for successful LUTS prevention strategies [12, 13]. Recalling peripartum LUTS is inaccurate when assessed remote from the delivery, resulting in high recall bias and measurement error [14]. Adequate representation of this important population is critical to establish confidence that the PLUS-BHS will allow valid inference to be made by future studies of this population.

Effect of mode administration is a well-documented phenomenon in survey research [15, 16]. In addition to context-based effects associated with mode of survey administration [17–20], other potential biases or sources of error associated with mode of administration are unknown. While a computer mode may increase efficiency of questionnaire completion, it also may produce measurement error. Thus, use of a computer may alter the distribution of PLUS-BHS [21, 22]. We intentionally include both paper and electronic modes in VIEW in order for the PLUS-BHS construction resulting from this validation process to be mode agnostic.

Measuring degrees of bladder health in a variety of settings requires a valid instrument, ideally self-administered, that can capture a spectrum from very healthy to very unhealthy. The PLUS Bladder Health Instrument (PLUS-BHI) item pool was generated using expert opinion, review and adaptation of existing instruments, and drafting of novel items to assess the elements of our conceptual model of bladder health. The items and language were refined by cognitive evaluation with community dwelling women and review of focus group data [10].

### Study populations

Inclusion criteria for the general and clinical center populations are outlined in Table 1. In general, non-pregnant, ambulatory women 18 yrs of age or older are targeted for enrollment.

**Table 1 Tab1:** Eligibility criteria for the general, clinical, and post-partum populations

General population	Clinical center population	Postpartum population*
*Inclusion criteria*		
Community dwelling Age ≥ 18 years old Female sex assigned at birth Fluent in written and spoken English Able to read and provide informed consent	Same inclusion criteria as general population *Additional criteria* Stand independently without human assist Able to stand and toilet independently Willing to complete PLUS-BHI validation survey and 2-day Bladder Health Symptom diary and 1-day Bladder Health Frequency-Volume diary prior to in-person clinical evaluation Willing to commit to an in-person evaluation within 8 weeks of enrollment	Same inclusion criteria as general and clinical populations *Additional criteria* Pregnant in 3rd trimester or less than 12 weeks postpartum Available and willing to come for an in-person evaluation within 8–12 weeks postpartum (may be enrolled prior to delivery)
*Exclusion criteria*		
	*Additional criteria* Pregnant at the time of data collection or within 12 weeks postpartum Diagnosis or history of bladder cancer, kidney transplant, pelvic radiation, or currently getting dialysis Current participation in a research study about bladder	Same exclusion criteria as the Clinical Population with the exception of being pregnant if enrolled in the 3rd trimester*

^*^Postpartum population eligibility is independent of mode of delivery (spontaneous vaginal, operative vaginal, and cesarean deliveries)

#### General population

The US Postal delivery sequence file (DSF), an address-based sample frame, is used to draw a random nationally representative sample. The DSF is the gold standard for address based sampling of US households with low coverage error [23]. In order to have geographic representation in terms of region of the country and across urban and rural continuum, a stratified sampling strategy was implemented with three nested sampling unit levels: primary sampling unit (PSU), secondary sampling unit 1 (SSU1) and a secondary sampling unit 2 (SSU2). The primary sampling unit mimics the PSU groupings used by the National Health And Nutrition Examination Survey (NHANES), [24] with states aggregated into one of five strata based on state health indicators. Each PSU is further divided between 0 and 2 times based on general geographic proximity (e.g., East, Midwest and West) resulting in a total of 11 SSU1 strata across the 5 PSUs (Table 2).

**Table 2 Tab2:** General population sampling SSU1 state grouping

SSU1 state grouping	States included
Group 1: PSU 1, West	HI, UT, WA
Group 2: PSU 1, Midwest	IA, MN, ND
Group 3: PSU 1, East	CT, MA, NH, NJ, NY, VT, RI
Group 4: PSU 2, CA	CA
Group 5: PSU 3, West	AK, AZ, CO, ID, MT, NM, OR, WY
Group 6: PSU 3, Midwest	IL, KS, ME, NE, SD, WI
Group 7: PSU 3, South	FL, VA
Group 8: PSU 4, TX	TX
Group 9: PSU 4, East	DE, IN, MD*, MI, OH, PA
Group 10: PSU 5, Western South	AR, LA, MO, NV, OK
Group 11: PSU 5, Eastern South	AL, KY, GA, MS, NC, SC, TN, WV

^*^DC counted in MD

PSU, Primary sampling unit; SSU, Secondary sampling unit

Each of the 11 SSU1 were further stratified as SSU2 according to the rural urban continuum codes (RUCC). These RUCC were categorized into four groups: urban (RUCC 1 and 2), suburban (RUCC 3, 4 and 6), rural city (RUCC 5 and 7), and rural (RUCC 8-9). A total frame of 6000 households (for a target of approximately 694 completed validation surveys) is randomly selected across sampling strata. Sampling is proportional across SSU1 state groupings, and equal across the 4 RUCC groups for a total of 44 sampling strata (Table 2).

#### Clinical center populations

The general clinical center population of women are being recruited from the community and medical practices surrounding the PLUS clinical research centers: Loyola University Chicago, University of Alabama at Birmingham, University of California San Diego, University of Michigan, University of Pennsylvania, Washington University in St Louis, and Yale University. Potential participants are screened on inclusion/exclusion criteria (Table 1) and purposive sampling conducted with the intention of representing the spectrum of bladder health and LUTS. To accomplish this, a modified version of the Patient Perception of Bladder Condition (PPBC) questionnaire is used to categorize participants into one of four equal size groupings [25]. Using the question “Which of the following statements best describes any problems you may have with peeing or your bladder?”: women are screened into healthy with no reported problems (PPBC response = 1), mild bladder problems (PPBC response = 2 or 3), moderate bladder problems (PPBC response = 4), or severe bladder problems (PPBC response = 5 or 6). When a quota is full (i.e., severe), individuals are screened out (Table 3).

**Table 3 Tab3:** VIEW target enrollment of clinical center population bladder symptom strata

Symptom strata	Self-report of LUTS-PPBC				
	Healthy	Mild	Moderate	Severe	Total
Frequency	90	15	15	15	45+
Incontinence		15	15	15	45+
Urgency		15	15	15	45+
Pain/discomfort		15	15	15	45+
Peeing/flow		15	15	15	45+
Urinary tract infection		15	15	15	45+
Total	90	88	88	88	354

LUTS, Lower urinary tract symptoms; PPBC, Patient perception of bladder condition: The four categories of Healthy to Severe map to PPBC responses to the question “Which of the following statements best describes any problems you may have with peeing or your bladder?”: healthy with no reported problems (PPBC response = 1), mild bladder problems (PPBC response = 2 or 3), moderate bladder problems (PPBC response = 4), or severe bladder problems (PPBC response = 5 or 6)

In order to ensure a sufficient representation across a spectrum of LUTS in the sample sites, a second level of screening is also employed using screening items assessing presence or absence of urinary frequency, urinary urgency, urinary incontinence, urinary pain, and difficulty voiding. Additionally, each center is required to enroll a minimum of 5 participants into each of the 4 age strata: 18–25, 26–45, 46–65, and 65+ years of age. For the postpartum population, women are recruited from 6 of the clinical centers during late pregnancy or around the time of delivery with the inclusion and exclusion criteria noted in Table 1. The timing of assessment of bladder health in the postpartum period is circumscribed to 6–12 weeks after delivery. Recruitment from the obstetric population is occurring simultaneously to those recruited from the clinical center population described above. Due to the limited age range and limited range of bladder health in the postpartum population, there are no specific age targets, or self-report of LUTS.

### Survey mode

The intended use of the validated PLUS-BHS is a self-administered questionnaire for women in general population research as well as in clinical research. Given the differing sampling approaches typically used for these different types of research, our goal is to ensure the PLUS-BHS is valid for use across two likely modes of administration: paper and pencil instrument (PAPI) and computer assisted instrument (CASI).

### Study administration

#### General population

The study flow for the general population cohort is outlined in Fig. 1. All households in the DSF sample frame are mailed a pre-notification letter including a $2.00 bill and a tri-fold color brochure describing the study, with a request for participation by the female in the household, age 18 or over with the most recent birthday. Households are randomized 1:2 to PAPI or CASI. The imbalanced randomization reflects an expected lower response rate from CASI [23]. For those randomized to PAPI, the first PLUS-BHI packet mailing includes $10 as incentive and a stamped envelope addressed to the Scientific and Data Coordinating Center (SDCC). Non-respondents are sent replacement packets up to 4 times. Those randomized to CASI are asked to provide a valid email address using the provided postage paid return envelope. Respondents who do not provide an email are necessarily assigned to the push-to-web group, wherein future paper mailings include an electronic link for online survey completion. Households who do provide an email address are randomized to either the push-to-web group or to receive an email with a link to the survey (referred to as the web primary group). This second randomization allows a full comparison of respondents who fully elect to respond via electronic mode to those who do not. Those in the web primary group are additionally randomized 1:1 to receive $5 thank you for providing an e-mail address. A total of four follow-up packets are mailed to non-respondent households wherein the final contact includes a paper version of the survey.

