**Fig. 1 Fig1:**
[figure not shown]
General population study flow. BHI, Bladder Health Instrument; CASI, Computer Assisted Self Interview; PAPI, Paper and Pencil self-Interview; RA, Random Assignment

Respondents, regardless of initial mode assignment, who fully complete the validation survey packet are subsequently re-contacted within 2–4 weeks and randomized 2:1 to complete either (a) a retest of the PLUS-BHI in the same mode (PAPI or CASI) followed by a 2-day bladder symptom diary (Additional file 1) or (b) to only complete a 2-day bladder symptom diary. The retest version of the PLUS-BHI includes 2 Guyatt transition rating items [26] to identify changes to a person’s health, which serve as an anchor for stability in the retest reliability analysis, as well as the PLUS-BHI items. The 2-day bladder symptom diary is mailed to the respondent independent of mode of PLUS-BHI completion. Up to 4 contact attempts are made for completion of the retest version of the PLUS-BHI and up to 3 contact attempts for completion of the 2-day bladder symptom diary. Respondents receive $10 compensation for completing each of the re-test and/or 2-day bladder symptom diary.

The NIDDK has an expectation of grant award recipients to support data sharing, facilitated by their data repository. To assess the impact of language related to data sharing in the consent process, each address is randomly assigned (1:1) to have the request for permission to share anonymized data with the NIDDK repository either at the end of the PLUS-BHI validation packet or to receive the request separately (e-mail for CASI, separate letter for PAPI). This allows for evaluation of potential threat bias influence on completion of the survey altogether and also the degree of endorsement separate from completion of the survey [23].

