### Strengths and limitations

One of the primary intended uses of the validated PLUS-BHS is to establish a U.S. general population estimate of women’s bladder health, across the life course. To ensure the PLUS-BHS is valid for this inference it is essential to validate using a national general population sample of women. Some of the challenges in conducting national population research is the identification of a representative sample frame, minimizing the well-known problem of coverage error. With survey methods sampling, the DSF with household level enumeration of every known mailing address within the U.S. is the address base sampling frame with the lowest coverage error that exists. The use of random assignment of both general population participants as well as, general clinical participants to the multiple modes (PAPI, CASI and within CASI Web primary as well as push to web) allows a valid and unconfounded comparison of differences in both response rate, item-response as well as distributional differences across mode. The inclusion of clinical samples using community based recruitment allows a clinical evaluation of women across the spectrum of potential bladder health. The inclusion of objective clinical test data provides the “hard ratings” required as a standard of evidence for valid inference with the intended use of the PLUS-BHS. A major strength of our validation work is the inclusion and evaluation of women during the postpartum period. While we would not expect women’s bladder health to be considered stable during pregnancy, we expect the postpartum period to be a factor in women’s bladder health over their lifetime.

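### In the general population sample the stated incentive and contact path change with assigned mode, so the PAPI versus CASI response-rate comparison is not unconfounded as claimed

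*Protocol article*

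**What the plan says.** The payments are in Study administration, General population. Every sampled household gets the same start: "All households in the DSF sample frame are mailed a pre-notification letter including a $2.00 bill". Then "Households are randomized 1:2 to PAPI or CASI". From there the arms differ.

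- **PAPI:** "For those randomized to PAPI, the first PLUS-BHI packet mailing includes $10 as incentive".
- **CASI:** households are first asked to return an e-mail address. "Respondents who do not provide an email are necessarily assigned to the push-to-web group". "Households who do provide an email address are randomized to either the push-to-web group or to receive an email with a link to the survey"; the latter is the web primary group. "Those in the web primary group are additionally randomized 1:1 to receive $5 thank you for providing an e-mail address". Households that do not respond get four follow-up packets, the last with a paper survey.
- **After the first survey, in either mode:** "Respondents receive $10 compensation for completing each of the re-test and/or 2-day bladder symptom diary".

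Strengths and limitations, referring to PAPI, CASI and the two CASI subgroups in both the general population and the general clinical sample, says that random assignment "allows a valid and unconfounded comparison of differences in both response rate, item-response as well as distributional differences across mode". The article does not mention the difference in payment there or elsewhere, or any allowance for it.

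**The concern.** The $10 is assigned by the same randomisation as paper mode. A higher response in PAPI could come from paper, from cash enclosed with the survey, from not having to return an e-mail address first, or from a mixture. The assigned-arm comparison is unbiased for the whole package, but the design as described cannot divide it into parts. Calling it unconfounded for response rate across mode claims more than that.

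Mode is not a side issue here. The Background makes evaluation of mode effects the second of two aims, and the Analysis plan lets a significant mode difference put an item up for removal. If payment changes which women respond, item distributions can differ between arms for a reason unrelated to the medium. The reported response difference may also guide the choice of mode in later population surveys.

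**Working it through.** **1. The plan's own figures.** The article gives no size for an incentive effect, so there is nothing to reproduce on that point. Its sample-size figure does reproduce (694/90 = 7.7 and (694 + 354)/90 = 11.6, stated as 8 and up to 12 participants per item) but has no bearing here.

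**2. Stated payment per household up to the first survey**

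Inputs, all from Study administration, General population: $2 to all; $10 to PAPI; $5 to half of web primary. The article does not give the share *e* of CASI households that supply an e-mail address, or the share *w* of those sent to web primary.

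- PAPI = 2 + 10 = $12.00.
- CASI average = 2 + 5 × 0.5 × *e* × *w*.

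| *e* (assumed) | *w* (assumed) | CASI average |
|---|---|---|
| 0.1 | 0.5 | $2.13 |
| 0.3 | 0.5 | $2.38 |
| 0.5 | 0.5 | $2.63 |
| 1.0 | 1.0 | $4.50 (ceiling) |

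The most any one CASI household receives is 2 + 5 = $7. Stated payments are therefore unequal by assigned mode whatever *e* and *w* are. The later $10 payments for retest and diary follow a completed first survey and do not depend on mode, so they do not equalise the first-survey incentive.

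**3. What the nested randomisation can recover**

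- Comparing web primary with and without the $5 estimates the effect of $5 within web primary. It says nothing about $10 sent with a paper survey.
- All households without an e-mail address go to push-to-web, so web primary and push-to-web are comparable only among e-mail providers. Among those, the web primary half without the $5 and the push-to-web half have the same stated payment, $2. That comparison is free of the incentive difference.
- No similar subset exists for PAPI versus CASI, because every PAPI household is sent the $10.

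**4. How small an incentive effect would be visible (illustration)**

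Of 6000 households, 6000 × 1/3 = 2000 are PAPI and 4000 are CASI. Target completes over addresses: 694/6000 = 11.6%. Suppose mode has no effect and incentive alone produces a difference *d*. Holding the overall rate at 11.6%, PAPI = 11.6% + 2*d*/3 and CASI = 11.6% − *d*/3. The two-sided test level of 0.05 is assumed; the article states none.

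| *d* (assumed) | Chance of a significant difference between modes |
|---|---|
| 1 point | 21% |
| 2 points | 62% |
| 3 points | 92% |

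This shows how sensitive the comparison is. It does not estimate the incentive effect.

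**The case against.** Five points on the other side deserve weight.

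- **Silence is not a statement.** A reader might infer that push-to-web households, and web primary households not drawn for the $5, are paid nothing. The article does not say so. It describes the $5 as thanks for an e-mail address, not as the CASI survey payment, and the article is condensed, with Fig. 1 not shown. This stands, and the point is limited to payments as described. An equal payment made later would still differ in timing from cash in the first packet.
- **The $5 is itself randomised.** A reader might infer that web primary versus push-to-web is confounded beyond repair. It is not: the $5 can be separated in analysis, and nothing in the article commits to pooling the two halves. This stands.
- **Item responses are a step removed.** A reader might infer that the item-level mode analysis is invalid, or that electronic administration could be rejected because of payment. Payment can reach item answers only by changing who responds. Removal is a matter for consideration, not automatic. The article has no rule for rejecting a mode. The general clinical sample is also randomised to mode, after enrolment, with prorated compensation up to $100 and no stated difference by mode. This stands and narrows the point considerably.
- **Response rate by mode is not a named objective.** It is absent from the Analysis plan, and the claim is in the Discussion. True, but it is made expressly for response rate.
- **Payment is one part of a bundle.** The e-mail request, mailing sequence and final paper copy differ too, so equal payment would not isolate mode. Correct, and a further reason why the comparison is one of strategies.

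**Conclusion.** The point holds for the response-rate claim in the general population sample. As described, assigned mode changes together with incentive ($12 for PAPI against an average of at most $4.50 for CASI) and with contact path. Randomisation therefore supports a valid comparison of assigned strategies, not an unconfounded comparison of mode.

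The payment inequality rests on one assumption: that the article lists all payments made up to the first survey. The size of any resulting difference in response is unknown. The illustration shows only that, with 2000 and 4000 households, an incentive effect of 2 to 3 points would often be read as a mode effect. The 11.6% in it is target completes over all sampled addresses, not a response rate among eligible women.

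For item responses the documents support a caution about respondent mix and no more. The sample-size rationale and the factor-analytic methods are not called into question.

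**What to change.** 1. **Wording.** In Strengths and limitations, limit the response-rate claim to the assigned strategy (mode with its incentive and contact path), and report general population PAPI versus CASI response in those terms. Cost: a sentence.
2. **Within CASI.** Compare web primary with push-to-web among e-mail providers only, using the web primary half not randomised to the $5, or keep both halves and adjust for the randomised $5. Cost: the first option halves the web primary arm in that comparison; the second keeps it but needs a model term.
3. **Items.** Before removing an item for a mode difference seen in the general population sample, check whether it also appears in the general clinical sample, among women actually randomised to mode. Women without e-mail there are offered PAPI, and postpartum women choose their mode. Cost: no new data, but the clinical sample is smaller (354), so failure to see a difference there is weaker evidence.
4. **Reporting.** If CASI households do receive a survey incentive, state its amount, timing and conditions. Cost: a sentence.

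Adding $10 to CASI mailings now is not advised. Recruitment is under way, so it would mix incentives within CASI over time and cost money, and the other differences in contact path would remain.
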